### Clinical study

#### Design

This study will be a prospective, randomized clinical trial to compare the clinical and radiological outcome between single screw cephalomedullary nailing (Gamma3) and integrated dual interlocking nailing (InterTan-IT) for the treatment of unstable (31A2_1–3_) intertrochanteric fractures. The paper complies with the Standard Protocol Items: Recommendations for Interventional Trials (SPIRIT) 2013 Statement for reporting of clinical trial protocols. The study is sponsored by the University of Patras Research Committee (ELKE) (University of Patras Campus, Rio, Greece). Ethical approval has been already acquired by the Ethics Committee of the University Hospital of Patras (approval number: 3373/7-2-2022) and the patients’ written consent will be obtained before participating in the study. The study is listed with the International Standard Randomized Controlled Trial Number (ISRCTN): https://doi.org/10.1186/ISRCTN15588442 (registered on 19/4/2022).

#### Primary objective

The *primary aim* of this study is to investigate if there are any significant differences in the main radiological measurements (cut-out, varus displacement, loss of reduction, malunion, nonunion) between Gamma3 and IT in closed unstable intertrochanteric fractures (31A2_1–3_) in patients aged over 70 years old at the 24-week follow-up evaluation.

The *second primary aim* would be the functional status at the 24-week follow-up using patient reported disease-specific scores (Harris Hip score HHS-and Oxford hip score-OHS).

#### Secondary objectives (Table 1)

**Table 1 Tab1:** Timeline chart of patient clinical evaluation

Outcome measure	Specification	Score	Assessment times				
			Pre-op	Post-op	6w	12w	24w
*Patient-reported outcome measures*							
EQ-5D-3L	General health status	5–15	√		√	√	√
SF-36	General health status	0–100	√		√	√	√
Elderly mobility scale	Fragility Assessment	0–20	√		√	√	√
SARC-F questionnaire	Sarcopenia assessment	0–10	√		√	√	√
NPRS	Joint pain	0–10	√	√	√	√	√
*Hip Joint-specific measures*							
Harris hip score (HHS)	Joint-specific score	0–100	√		√	√	√
Oxford hip score (OHS)	Joint-specific score	0–100	√		√	√	√
*Surgeon and patient related complications*			Intra-op	Post-op	√	√	√
Failure rates				Post-op	√	√	√

*NRPS* numerical pain rating scale, *SF-36* short-form 36, *EMS* elderly mobility scale, *SARC-F* strength, assistance with walking, rising from a chair, climbing stairs, and falls questionnaire, *HHS* Harris hip score, *OHS* Oxford hip score

Several secondary objectives will also be studied to evaluate the effectiveness and safety of the devices by quantifying and drawing presumptions from observed differences between treatment groups in the following:Comparison of perioperative and intraoperative surgical data (age-adjusted Carlson Comorbidity Index [41], operation time, fluoroscopy time and dosage, blood loss, length of hospital stay, prescription of pain-killers, osteoporosis assessment using postoperative DEXA of the unaffected hip, union time and intraoperative surgeon related complications, including lag screw malposition, propagation of the fracture, non-anatomical reduction, varus/valgus deformity, rotational deformity and tip-apex distance-TAD).Pain level at the perioperative period and at 6-, 12-, and 24-weeks postoperatively using the visual analogue scale (VAS) Pain Score.Patient reported general health status prior to surgery and at 6-, 12- and 24-weeks post-surgery using the SF-36 form, the EQ-5D-3L Questionnaire, the SARC-F Index and the Elderly Mobility Scale (EMS).

#### Patient selection

The patients that will take part in the study, are those over 70 years old, admitted in the Orthopaedic Clinic of the University Hospital of Patras, Greece, suffering from a closed unstable (31A2_1–3_) intertrochanteric fracture. Those patients will be randomized in two groups (Gamma3 and IT). The pre-operative data will be comprised of demographic information, radiological examination of the hips and other questionnaires to conclude the overall physical health and mobility prior the fracture. The participants will be free to withdraw from the study or the investigator can withdraw a patient. If a participant withdraws, they will be listed to a “Change of Status” form and will be invited to present for an endpoint follow-up (Fig. 4).

**Fig. 4 Fig4:**
[figure not shown]
Flowchart of the clinical study

#### Eligibility criteria

Closed intertrochanteric fracture (AO/OTA:31A2).Age over 70 years.Presentation to hospital within 7 days of injury.No concomitant injuries or prior operations to the unaffected hip.

#### Exclusion criteria

Concomitant injuries affecting treatment or rehabilitation of the affected limb.Associated neurovascular injuries requiring immediate surgery.Patients with limited Greek proficiency including family members.Patients where consent is refused.Patients with severe dementia, non-ambulated and with severe associated diseases prohibiting operative intervention.

#### Sample size

This study will use two primary clinical outcome measures namely the Oxford Hip Score and the Harris Hip Score. The minimum clinically important differences (MCIDs) for the HHS have been estimated between 7 and 10, whereas for the OHS between 5 and 7. The aim will be to recruit 78 patients in each group as this will provide sufficient participants to obtain a power of 90% for both primary clinical outcome measures. With an allowance for 15% drop-out, the total number of patients required will be 194 (97 in each group). If recruitment proves to be problematic during the course of the trial, then the target will be lowered and the more usual 80% power level will be considered sufficient. For this scenario, the total number of patients required will be 140 (including 15% for drop-out).

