## Introduction

Hip fractures are an increasingly common consequence of falls in older people that are associated with a high risk of death and reduced function [1, 2]. In fact, hip fractures constitute one of the most common impairments worldwide in terms of loss in disability-adjusted years for people older than 60 years old [1, 3]. The absolute number of hip fracture hospitalizations in the US are estimated to approach 289,000 in 2030 with an expected increase to 4.5 million by the year 2050 [4, 5]. In the UK, there is an ongoing age-standardized fall of hip fractures of 0.5% per year, but it is estimated that the annual incidence will double in the next 25 years [6]. The consequences for hip fractures in elderly individuals are significant in terms of lives lost and the associated negative impacts on hip fracture patients’ functioning and quality of life [7, 8]. In a recent critical review of 38 studies by Dyer et al. [1], hip fracture survivors experienced significantly worse mobility, independence in function, health, quality of life and higher rates of institutionalization than age matched controls. Even with integrated, multidisciplinary models for the treatment of hip fragility fractures the in-hospital mortality rate was 2.4%, and the overall mortality at 1 year from the intervention 18.7%; full mobility status or a low impairment of mobility was reached 32.1% of patients [9]. The reported mortality rate at 1 year in a very recent study from the Swedish Hip Fracture Registry [10] was approximately 20% for women and 30% for men in a total population study of 289,603 first hip fractures during a 20-year-old period (1998–2017).

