#### Randomization

Randomization sequence will be created using Stata 9.0 (StataCorp, College Station, TX) statistical software and will be stratified with a 1:1 allocation ratio using random block sizes of 2, 4, and 6. An investigator not involved in the main study will perform the randomization process. These data will be stored on computer and will be available at the day of the intervention.

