### Statistical analysis

The primary outcome measure of device radiological failure is considered a binary outcome (device failed/did not fail). A binary logistic regression model will be performed to assess the association between the outcome of device failure and the predictor of device type (Gamma3, Intertan). The complication rate of G3 versus InterTan at 24 weeks post-operatively would be compared using a chi-squared (at the 5% level). The differences between HHS and OHS between groups will be assessed using an independent samples *t* test at 24 weeks postoperatively at the 5% level. Test levels, will be adjusted using the methods of Holm-Bonferroni to allow for the multiple comparisons. A linear regression analysis will also be used to quantify the effects of the treatment groups on each of the primary outcome measures, after adjusting for the effects of a range of other important, potentially confounding, factors (e.g. age, gender) recorded for each patient.

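### The 194-patient target does not follow from 78 per group and 15% drop-out, while the 140-patient fallback does, so the two targets rest on different inputs

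*Protocol article*

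**What the plan says.** All the figures stand in one paragraph, Clinical study, Sample size. The base number is "The aim will be to recruit 78 patients in each group as this will provide sufficient participants to obtain a power of 90"% for both hip scores. The inflated number follows at once: "With an allowance for 15% drop-out, the total number of patients required will be 194 (97 in each group"). If recruitment is difficult, "then the target will be lowered and the more usual 80% power level will be considered sufficient", and for that case "the total number of patients required will be 140 (including 15% for drop-out").

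The Randomization section confirms equal groups ("stratified with a 1:1 allocation ratio using random block sizes of 2, 4, and 6"). The Statistical analysis section says that the hip scores will be "assessed using an independent samples *t* test at 24 weeks postoperatively at the 5% level", without stating one-sided or two-sided, and adds a Holm-Bonferroni adjustment. No second inflation factor appears anywhere in the article. The Discussion speaks only of about 200 patients.

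**The concern.** A reader who inflates 78 by 15% does not arrive at 97 by either of the usual conventions. Both recruitment targets carry the same 15% label, so one would expect both to come from the same base number and the same allowance. If they do not, it is unclear how many evaluable patients the trial is planned to have, what loss it is planned to withstand, and whether the reduced target is a like-for-like step from 90% to 80% power. The fallback is a real contingency in the plan, so its derivation matters as well as that of the main target.

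**Working it through.** **Inputs.** From Sample size: 78 per group at 90% power; 15% drop-out; 97 per group, 194 in total; fallback 140 in total at 80% power, also 15%. From Randomization: 1:1 allocation. From Statistical analysis: *t* test at 5%. Assumption: the test is two-sided. The 78 is read as the evaluable number, since the drop-out allowance is added to it.

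**Step 1: the main target.**
- Dividing by the retained fraction: 78/(1 − 0.15) = 91.8, so 92 per group and 184 in total. Inflating the total gives the same: 156/0.85 = 183.5, so 184.
- Multiplying instead: 78 × 1.15 = 89.7, so 90 per group and 180 in total.
- Stated: 97 and 194. Neither convention reproduces it. The excess over 184 is 10 patients, or 10/184 = 5%.

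**Step 2: what 97 would mean.**
- With 78 held fixed, the loss is 1 − 78/97 = 19.6%.
- With 15% held fixed, the evaluable number is 97 × 0.85 = 82.45, about 82 per group. Going forward, 82/0.85 = 96.5, so 97 per group and 194 exactly.

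**Step 3: the fallback.** No SD is given, but it cancels when 78 is scaled from 90% to 80% power at the same effect:
- ratio = [(1.960 + 0.842)/(1.960 + 1.282)]² = 0.747
- 78 × 0.747 = 58.3, so 59 evaluable per group
- 59/0.85 = 69.4, so 70 per group and 140 in total. The stated figure is reproduced.

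With the inputs that would explain 194, the fallback would differ:
- 19.6% loss: 59 × 97/78 = 73.4, so 74 per group and 148 in total.
- 82 evaluable at 15%: 82 × 0.747 = 61.25, so 62; 62/0.85 = 72.9, so 73 per group and 146 in total.

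**Step 4: sensitivity to the test level.**

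| Test | Evaluable n at 80% | Total at 15% | Total at 19.6% |
|---|---|---|---|
| Two-sided 5% | 59 | 140 | 148 |
| Two-sided 2.5% | 60 | 142 | 150 |
| One-sided 5% | 57 | 136 | 142 |

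**Step 5: effect on power.** 78 per group at 90% and two-sided 5% implies a standardised difference of about 0.52. At that effect:
- 82 evaluable per group (97 at 15% loss) gives about 91% power.
- 59 evaluable per group (70 at 15% loss) gives about 80% power.
- 56 evaluable per group (70 × 78/97 = 56.3) gives about 78% power.

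These powers are before any Holm adjustment.

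**The case against.** The strongest reply is that nothing the article promises fails under its own printed assumptions. At 15% loss, 97 per group leaves about 82 evaluable and about 91% power against the stated 90%, and 140 delivers its 80%. That stands, and it is why the point is minor.

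A reader might go further and infer that the main target conceals a 20% allowance. The documents do not establish this. The article never mentions 20%, and 82 evaluable per group at the stated 15% also gives exactly 97. That second reading fits the fallback less well (146 rather than 140), but it cannot be excluded. Nor does a round 20% repair the sum: 78/0.80 = 97.5, which rounds up to 98 per group and 196.

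A reader might also infer that 15% is too low, because the Introduction cites one-year mortality of 18.7% and, from a national registry, "approximately 20% for women and 30% for men". This shows no contradiction. Those figures describe broader hip-fracture populations over a year, whereas this trial follows patients for 24 weeks and excludes severe dementia, non-ambulant patients and severe disease prohibiting surgery. Converting one to the other needs a hazard assumption that the article does not supply. Whether 15% is prudent is a planning judgement, separate from the arithmetic.

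Finally, the fallback's evaluable number is not printed, so Step 3 is a back-calculation. It rests on a two-sided test; an unstated one-sided 5% test would bring the 19.6% allowance near 140 (142). The error in the main target does not depend on this.

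**Conclusion.** The main target is wrong as written: 78 per group with 15% drop-out gives 92 per group and 184 in total, not 97 and 194. This is arithmetic on printed figures and needs no assumption. That the fallback rests on different inputs is an inference, firm under a two-sided test: 140 comes from 78 at a true 15%, and neither explanation of 194 leads to it. Which of the 78, the 15% or the 194 is the slip cannot be determined from the article.

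The size is 10 patients, about 5%, in the direction of over-recruitment. The stated power of the main target is not reduced. The fallback would fall short, at about 78% rather than 80%, only if losses were near 19.6%, which the article does not state. It would be wrong to conclude from this that the trial is underpowered.

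**What to change.** Reconcile the 78, the 15% and the 194 in the Sample size section, and derive both targets from the same inputs.

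- If 78 and 15% are meant: restate the main target as 184 (92 per group) and leave 140 unchanged.
- If 194 is to stay with 15%: state that it leaves about 82 evaluable per group and about 91% power, and either derive the fallback from the same base number (146) or say that 140 is derived from 78.
- If 194 is to stay with 78: state the allowance as 19.6%, and restate the fallback on the same allowance as about 148, or keep 140 and state about 78% power.

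State the sidedness and test level used, so that the step from 90% to 80% power can be checked. The cost is a few words and one or two figures; recruitment need not change if 194 is kept.

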#### Randomization

Randomization sequence will be created using Stata 9.0 (StataCorp, College Station, TX) statistical software and will be stratified with a 1:1 allocation ratio using random block sizes of 2, 4, and 6. An investigator not involved in the main study will perform the randomization process. These data will be stored on computer and will be available at the day of the intervention.

#### Concealment mechanism

For each surgical session patient details and the randomized treatment will be sealed in an opaque envelope that will be given to the coordinated nurse just before the start of the intervention. The patients, relatives, investigators, nurses, and all relevant personnel would be blinded to the indented treatment. The envelope will be opened by the coordinated nurse after the patient is sedated and placed to the radiological table, the hip is properly prepared and the surgeons are ready to apply the intervention. Both instrumentations for Gamma3 or IT would be available at the operative room. After opening the envelope, the procedure will be unblinded for all participants.

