**Discussion:**

This study will be the first to compare clinical, radiological and biomechanical measurements of the two different cephalomedullary nails. Our main hypothesis is that the IT nail would provide better radiological outcome and probably better clinical results than the Gama3 nail.

*Clinical trial registration* International Standard Randomized Controlled Trial Number (ISRCTN): https://doi.org/10.1186/ISRCTN15588442, registered on 19/4/2022.

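### The protocol lifts blinding for all participants once the envelope is opened and never restores it for patients, leaving the primary HHS and OHS comparisons open to avoidable expectation bias

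*Protocol article*

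**What the plan says.** All references are to the protocol article.

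- **Before allocation is revealed** (Concealment mechanism): "The patients, relatives, investigators, nurses, and all relevant personnel would be blinded to the indented treatment".
- **When it is revealed** (same section): "The envelope will be opened by the coordinated nurse after the patient is sedated and placed to the radiological table".
- **Afterwards** (same section): "After opening the envelope, the procedure will be unblinded for all participants".
- **Outcomes exposed.** Under Primary objective, the second primary aim "would be the functional status at the 24-week follow-up using patient reported disease-specific scores", meaning HHS and OHS. Under Sample size: "This study will use two primary clinical outcome measures namely the Oxford Hip Score and the Harris Hip Score".
- **Expectation** (Abstract, Discussion): "Our main hypothesis is that the IT nail would provide better radiological outcome and probably better clinical results than the Gama3 nail".
- **Analysis** (clinical Statistical analysis section): HHS and OHS are compared at 24 weeks by an independent-samples t test at 5%, with Holm-Bonferroni adjustment of the test levels. A linear regression adjusts for factors such as age and gender.

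**The concern.** The operating team has to know which nail is going in, and anyone reading the radiographs will see it. Neither reason applies to a sedated patient, to relatives, or to whoever hands out the questionnaires. The timing of the envelope makes it possible to keep the patient unaware, and the next step in the protocol gives that up.

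The outcomes affected are subjective: HHS and OHS first, then pain, SF-36 and EQ-5D-3L. Where answers can be coloured by knowledge of the implant, and the team has said which implant it favours, a difference in scores can arise without any difference in hip function. Such a shift acts on the outcome itself and differs by arm. A t test reads it as treatment effect, and adjusting for baseline covariates leaves it in place. What is at stake is whether a modest difference in HHS or OHS could be credited to the nail.

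**Working it through.** **1. Textual check.** The documents give no figure for this point, so the first step is to compare the sections.

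| Section | Bearing on blinding after surgery |
|---|---|
| Concealment mechanism | Patients and relatives are named among the blinded; blinding then ends for all participants |
| Patient selection; Surgical intervention | The word participant is used for enrolled patients (withdrawal, physical therapy) |
| Radiographic evaluation | Two examiners; no blinding stated |
| Outcome assessment; Follow-up assessments | Questionnaires and films at 6, 12 and 24 weeks; nothing on who knows the nail or in what order they are done |
| Statistical analysis (clinical) | No mention of blinding |
| Limitations | Lack of blinding is not listed |

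No section restores blinding for patients, and none gives a reason for lifting it from them.

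**2. Illustration of size.** The bias values are assumptions; the documents supply none.

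Inputs: n = 78 per group and 90% power (Sample size); 5% level, t test and Holm-Bonferroni (Statistical analysis). Two-sided testing is assumed because sidedness is not stated. The assumed bias b is 0.1 or 0.2 SD, with no true effect.

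The test statistic follows a noncentral t with 2 × 78 − 2 = 154 degrees of freedom and noncentrality b × √(n/2), where √(78/2) = 6.245:

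- b = 0.1: noncentrality 0.62
- b = 0.2: noncentrality 1.25

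Rejection probability = P(|T| > critical value):

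| Test level | Critical value | No bias | b = 0.1 SD | b = 0.2 SD |
|---|---|---|---|---|
| 5% | 1.98 | 5% | 9.5% | 23.7% |
| 2.5% (first Holm step, two tests) | 2.26 | 2.5% | 5.5% | 15.8% |
| 1.67% (first Holm step, three tests) | 2.42 | 1.67% | 3.9% | 12.4% |

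**3. The same bias in score points.** With 78 per group, 90% power and two-sided 5%, the detectable difference is 0.522 SD. The article gives no SD. If its minimum clinically important differences (MCIDs) are taken as the design differences:

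- HHS: SD = 7/0.522 to 10/0.522 = 13.4 to 19.1 points (unrounded divisor). The bias is then 0.1 × 13.4 = 1.3 up to 0.2 × 19.1 = 3.8 points.
- OHS: SD = 5/0.522 to 7/0.522 = 9.6 to 13.4 points. The bias is then 0.1 × 9.6 = 1.0 up to 0.2 × 13.4 = 2.7 points.

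These shifts are 0.1/0.522 = 19% to 0.2/0.522 = 38% of the MCID. A bias well below a clinically relevant difference would still move the rejection rate noticeably. The rates in step 2 do not depend on the back-calculated SD.

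**The case against.** **The sentence may cover only those in theatre.** Its subject is the procedure, and the surrounding sentences concern the nurse, the surgeons and the operating room. It does not say that patients will be told their nail. This reading is possible but less natural: the same section counts patients among the blinded, and elsewhere the article uses participant for enrolled patients. On the narrow reading there is still no statement that patients stay unaware, so the sentence needs rewording either way.

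**A reader might infer that unblinding patients serves no purpose.** The documents do not support that. They give no reason, which is silence rather than proof; telling patients about an implanted device could be one. What stands is that no reason is stated.

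**A reader might take 10% to 24% as the trial's false-positive rate.** That goes too far. The bias is assumed, and nothing shows that patients themselves prefer either nail; both groups get the same physical therapy, and the stated expectation is the investigators', hedged on clinical results. The 5% level also leaves out the planned Holm-Bonferroni step, which gives lower absolute rates. The inflation relative to the nominal level remains.

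**Reach is limited.** Radiological failure is the first primary aim, and the nail is visible on the films, so that outcome cannot be protected in this way. This stands.

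**Staffing.** This is one hospital clinic, and the article does not say whether staff who were not in theatre are available for questionnaires. This also stands, so separate staff can be asked for only where feasible.

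**Conclusion.** The point holds as a stated design choice that lets avoidable expectation bias into the functional comparison. It rests on three things the article says: blinding ends for all participants when the envelope is opened, patients are sedated at that time, and HHS and OHS are primary and drive the sample size. It also rests on finding no later provision that keeps patients unaware.

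The size of the bias is unknown. The rejection rates above show only sensitivity to an assumed shift of 0.1 to 0.2 SD with two-sided tests and no true effect; they are not estimates for this trial. The trial can run as written, but no later analysis could separate such a bias from an effect of the nail, so the change should be made. Confidence is medium, because the sentence has a second reading and a fuller protocol may say more.

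**What to change.** Replace the last sentence of Concealment mechanism with wording to this effect:

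- Only the theatre team and the radiograph readers are unblinded.
- Patients and relatives are not told the nail type until after the 24-week visit, with disclosure possible on clinical need.
- At each visit HHS, OHS and the other questionnaires are completed before the films are viewed and, where existing staffing allows, with staff who were not in theatre.
- At 24 weeks patients are asked which nail they think they received, so that the success of blinding can be reported.

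**Cost.** Protocol and consent wording, the order of tasks at visits, and one extra question. Sample size, treatment and visit schedule do not change. Separate questionnaire staff may need resources the article does not describe, hence the condition.

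**Downside.** Patients learn their implant type later, and the radiological outcome remains unblinded; the article should say so under Limitations.
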